### 4.2. Electromyographic Recording

Pre-gelled adhesive bipolar electrodes will be placed by feeling the muscle and considering the direction of the muscle fibres according to Abarrotar’s criteria [22]. The same electrode positions will be used during all recording sessions:The ground electrode will be placed on the clavicle.The electrodes corresponding to the first channel will be placed on the common extensor digitorum on the posterior aspect of the forearm, with a distance between them of approximately 2 cm (Figure 3).The electrodes corresponding to the second channel will be placed on the common deep flexor digitorum on the anterior aspect of the forearm, with a distance between them of approximately 2 cm (Figure 4).The reference electrode will be placed over the biceps brachii.

### 4.3. Data Analysis

The data will be entered into a database, where each subject will be assigned a number and will not be linked to any data that could identify them, guaranteeing their anonymity. Data analysis will be performed by an external statistician using SPSS Statistics for Windows v.28.0 (IBM Corp, Armonk, NY, USA). The most appropriate tests will be established according to the characteristics of the distributions such as descriptive, correlational, and multivariate analyses. An alpha value of 0.05 is established as the level of significance.

## 5. Expected Results

This study will test whether MI and AO activate flexor and extensor muscles of the wrist and fingers in stroke patients. Furthermore, it will try to determine if this activation is related to different factors such as image evocation, the degree of independence in daily life activities, the functionality of upper limbs, age, or gender.

### 5.1. Strengths and Weaknesses of the Study

The strong point of this study is the systematisation of an electromyographic recording protocol of the upper limbs, which allows us to determine whether specific neurorehabilitation tools provoke activation not only at the cortical level but also as a natural response at the muscular level. This is fundamental, as the literature shows the need for more research on EMG analysis in the upper limbs, as well as the need to establish a methodology and a standardised protocol [23].

Previous studies have shown the activation of different brain areas during MI: the precentral gyrus of the primary motor cortex [24], the premotor area [25], the corpus callosum [26], the parietal cortex [27], the cerebellum [28], and the basal ganglia [29]. During AO, Broca’s area and the premotor cortex [30], the inferior parietal cortex [31], the superior temporal cortex [32], the superior parietal cortex [33], the temporoparietal junction [34], and the basal ganglia [35] are activated. Knowing what the muscular response is in people who have suffered a stroke will allow us to improve the therapeutic indications for these patients.

Furthermore, knowing whether the muscular activation caused by MI or AO is related to the mental evocation capacity, the degree of independence in ADLs, upper limb functionality, quality of life, cognitive impairment, gender, or age will allow us to adopt the most appropriate intervention in each case and thus achieve the best functional recovery.

On the other hand, scientific evidence of the benefits of neurorehabilitation treatment tools focused on the person with stroke will increase the empowerment and safety of patients, as well as their perspective and that of their family towards treatments.

Another strength of this protocol is that it has taken into account certain aspects that have already been demonstrated in other studies. Repeatedly imagining different movements can lead to mental fatigue, affecting motor performance [36]. Therefore, it is essential to control the duration of the recordings and the number of movements and repetitions when designing protocols. In the case of AO, protocols and studies that have been carried out using EMG have shown that muscle activation occurs, and, after training, changes in the contraction of the muscles were studied [37,38]. However, these studies have not been conducted in the therapeutic field, so demonstrating that protocols of this type are effective may open doors in neurorehabilitation.

In terms of limitations, the main limitation may be the number of muscles evaluated, limited by the recording system to be used. It would be interesting to be able to record electromyographic activity in the contralateral limbs. Another limitation may be the convenience sample and its regional context. Furthermore, the heterogenicity of strokes could impact data generalisation. As it is an exploratory intervention, participants adherence can be influenced.

Finally, the analysis of the correlation between the electromyographic response by age may be limited by the smaller number of subjects expected due to the prevalence of stroke in those under 60 years of age.

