The secondary objectives are as follows:To describe the muscle activation in the wrist and finger flexors and extensors that occurs during the use of the CEMIMA as a motor imagery tool via surface electromyographic recordings.To describe, using surface electromyographic recordings, the muscle activation in the wrist and finger flexors and extensors that occurs during the application of action observation.To analyse whether there are differences between the subjects who evoke better or worse mentally depending on their electromyographic response in MI and AO.To analyse the association between the degree of independence in ADLs, upper limb functionality, quality of life, mental evocation, and cognitive impairment with the electromyographic response during MI and AO.To analyse, from a gender perspective, the determinants of the study in men and women.To study whether there is a relationship between the electromyographic response during MI and AO by age or age groups (over 65 years).

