### 2.4. Power Calculation and Sample Size

It is estimated that to conduct a study using linear regression tests for each predictor, considering an effect size between 0.5 and 0.8, a statistical power of 90%, and a safety level of 95% and taking into account the variance of a previous pilot study conducted, between 21 and 28 subjects will be required.

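### Associations of patient factors with the MI and AO responses cannot guide a choice between MI and AO unless each factor is also related to the MI-minus-AO difference, which this protocol nowhere names

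*Protocol article*

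**What the plan says.** **The intended use.** Section 5.1 starts from "knowing whether the muscular activation caused by MI or AO is related to the mental evocation capacity", adds independence in daily activities, arm function, quality of life, cognition, gender and age, and concludes that this knowledge "will allow us to adopt the most appropriate intervention in each case and thus achieve the best functional recovery".

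**The stated analyses.** Four places bear on them:
- Secondary objective 3 (section 1) is "To analyse whether there are differences between the subjects who evoke better or worse mentally depending on their electromyographic response in MI and AO".
- Secondary objective 4 relates independence, arm function, quality of life, "mental evocation, and cognitive impairment with the electromyographic response during MI and AO". Objectives 5 and 6 take up gender and age, the latter again in terms of the response during MI and AO.
- Section 5 says that "it will try to determine if this activation is related to different factors such as image evocation" and several others.
- Section 2.4 sizes the study "to conduct a study using linear regression tests for each predictor", giving 21 to 28 subjects. Section 4.3 names only broad classes of analysis (descriptive, correlational, multivariate) and a significance level of 0.05.

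**The design.** Under section 4.1 each participant attends three weekly sessions: control, MI and AO. An MI-minus-AO difference can therefore be formed for every participant.

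**The concern.** Two different questions are in play. The objectives ask whether a factor goes with a larger or smaller EMG response under MI and under AO. Section 5.1 draws a conclusion about which intervention suits which patient. If the candidates are MI and AO, the second question is whether the factor changes the difference between them.

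A factor can be clearly associated with both responses and be no help in choosing. It can also reach significance under one technique and miss it under the other by chance, which invites the conclusion that it favours the first. In the other direction, a factor with opposite effects under the two techniques can be missed by within-technique tests although the paired data would show it. At stake is an unsupported statement about who should receive MI and who AO.

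**Working it through.** **The two null hypotheses.** For a factor x, write the responses of one person as

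- Y_MI = a1 + b1·x + e1
- Y_AO = a2 + b2·x + e2
- D = Y_MI − Y_AO = (a1 − a2) + (b1 − b2)·x + (e1 − e2)

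An association with the response in each technique tests b1 = 0 and b2 = 0. A choice between techniques depends on b1 − b2, the slope of D on x. When b1 = b2 ≠ 0, both within-technique nulls are false and b1 − b2 is still zero.

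**The plan's own figure.** Section 2.4 gives 21 to 28 subjects for effect sizes of 0.5 to 0.8 at 90% power. The effect metric, number of predictors and pilot variance are not given. Read as Cohen's f² at two-sided 5%, 0.5 and 0.8 need 24 and 16 subjects with one tested predictor, and 29 and 20 with two. The range is neither confirmed nor refuted. It is used below only as the sample size.

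**Inputs.** From the document: n = 21 and 28, and alpha 0.05. Assumed, because the document gives no value: two-sided tests, normal data, the same factor-response correlation r in both techniques (0.3 to 0.6), and MI-AO residual correlation ρ (0.3 to 0.7). There were 40,000 simulated studies per setting.

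**Equal slopes: percentage of studies in which exactly one technique is significant**

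| n | r | ρ = 0.3 | ρ = 0.5 | ρ = 0.7 |
|---|---|---|---|---|
| 21 | 0.3 | 32.1 | 27.1 | 21.2 |
| 21 | 0.4 | 38.4 | 32.9 | 24.9 |
| 21 | 0.5 | 34.1 | 28.8 | 22.1 |
| 21 | 0.6 | 19.5 | 16.7 | 12.9 |
| 28 | 0.3 | 36.5 | 30.8 | 23.5 |
| 28 | 0.4 | 38.1 | 31.5 | 24.4 |
| 28 | 0.5 | 25.2 | 21.8 | 16.7 |
| 28 | 0.6 | 8.9 | 8.0 | 6.4 |

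Allowing for simulation error, and for repeat runs that reached 39%, the range is roughly 6 to 39%. The test of D on x was significant in 4.8 to 5.2% of studies in every setting.

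**Power of the paired test when slopes differ.** With unit-variance responses, Var(e1 − e2) = (1 − b1²) + (1 − b2²) − 2ρ√[(1 − b1²)(1 − b2²)], and the correlation of x with D is (b1 − b2)/√[(b1 − b2)² + Var(e1 − e2)].

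- *Slopes 0.5 and 0.2, ρ = 0.5.* Var(e1 − e2) = 0.75 + 0.96 − √(0.75 × 0.96) = 0.861. The correlation is 0.3/√(0.09 + 0.861) = 0.31. Simulated power is 28% (n = 21) and 36% (n = 28).
- *Slopes +0.35 and −0.35, ρ = 0.5.* Var(e1 − e2) = 0.8775. The correlation is 0.7/√(0.49 + 0.8775) = 0.60. Simulated power is about 86% and 94%, against about 36% and 46% for each within-technique test. This is a favourable case and should not be taken as typical.

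**The case against.** **The tests are left open.** Section 4.3 fixes no model, and a repeated-measures model with a factor-by-condition term would fit under multivariate analyses. A reader might infer that the study will run only separate within-technique tests and never examine the difference. The document does not support that: section 2.4 does not define the regression outcome, and an analysis plan may exist. What stands is narrower. The document names no such contrast, and section 5.1 draws its conclusion from relation to activation, not from an interaction.

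**The choice may not be MI against AO.** A reader might also infer that section 5.1 promises a rule for choosing between the two. Its wording allows another reading: who is a candidate for these techniques at all. Section 1 ties their benefit to evocation ability and presents them as alternatives when other techniques are not possible. For that purpose a factor acting equally on both is informative. This stands, so the point is conditional on the MI-or-AO reading. No decision rule based on significance in one technique is stated either.

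**The size depends on assumptions.** If the effect sizes of 0.5 to 0.8 in section 2.4 are f², then r = √[f²/(1 + f²)] is 0.58 to 0.67, and exactly one technique is significant in about 6 to 23% (n = 21) or 2 to 12% (n = 28) of studies. So strong shared effects make split results less common, at times below 5%. They then mostly show as significant in both techniques, which still says nothing about which to prefer.

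**An apparent error rate that is not one.** At r = 0.5 and ρ = 0.5, at least one technique is significant in 81% (n = 21) or 91% (n = 28) of studies. A reader might take this as a false-positive rate. It is power to detect an association that is real by construction.

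**Conclusion.** The concern holds in a limited form. The conclusion in section 5.1 does not follow from the associations stated in sections 1 and 5 if it means choosing between MI and AO. That follows from the two null hypotheses and needs no numerical assumption. The size does: roughly 6 to 39% of studies with a split result under equal slopes, against 5% for the paired test, for r between 0.3 and 0.6, ρ between 0.3 and 0.7, normal data and two-sided 5% tests.

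The paired test would not settle the matter at this sample size unless slopes differ widely. Nor would it support the closing claim about functional recovery: the outcome is EMG, recorded in one session per condition, and recovery after treatment is not measured. The change is worth making because it is cheap and matches the analysis to the stated use. It does not call the descriptive objectives into question.

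**What to change.** 1. For each factor in secondary objectives 3 to 6, add the regression of the within-person MI-minus-AO EMG response on the factor, or equivalently the factor-by-technique interaction in one repeated-measures model. Measure the response on the same scale in both conditions.
2. Report the slope difference with its 95% CI and label the contrast exploratory.
3. Describe the separate MI and AO associations as showing who responds, not which technique to prefer.
4. In section 5.1, say whether the intended choice is between MI and AO or about candidacy for either. On both readings, limit the sentence to EMG response and drop the inference to functional recovery.

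The cost is one more regression per factor and EMG outcome, on data already to be collected, plus a few lines of wording. The downside is low power for moderate slope differences. Most intervals will be wide, and fewer factors will be reported as relevant to choosing a technique.

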### 5.2. Contribution to Occupational Therapy and Physiotherapy

Scientific knowledge in the disciplines of health sciences has been linked to academic recognition in different parts of the world. Until ten years ago, in Spain, physiotherapists, occupational therapists, and nurses were not able to start a research career by a purely natural route. This has happened in other parts of the world, and in some countries today, physiotherapists and occupational therapists are not recognised as having the ability to perform research. The results of this study will contribute to the development of these disciplines in the field of neurorehabilitation.

### 5.3. Ethics and Dissemination

The study is authorised by the Ethics Committee for Research with Medicines of the Salamanca Health Area and follows the principles of the Declaration of Helsinki. All subjects will be informed of the objectives of the project and the risks and benefits of the examinations to be performed and will sign a corresponding informed consent form. No risk or discomfort is foreseen with applying any of the experimental conditions.

All the information on this study will be coded and anonymised according to the corresponding Data Management Plan. The informed consent forms will be kept in the facilities of the NEURORREHABILITACION (APSF-19)-NEUROUSAL research team following current legislation (Organic Law 3/2018 of 5 December on Personal Data Protection and Guarantee of Digital Rights and Regulation (EU) 2016/679 of the European Parliament and of the Council of 27 April 2016 on Data Protection, RGPD).

## Figures and Tables

**Figure 1 sensors-24-01802-f001:**
[figure not shown]
Records 1 and 2.

**Figure 2 sensors-24-01802-f002:**
[figure not shown]
Schedule of experiments.

**Figure 3 sensors-24-01802-f003:**
[figure not shown]
Electrode placement scheme for extensor muscles.

**Figure 4 sensors-24-01802-f004:**
[figure not shown]
Electrode placement scheme for flexor muscles.

**Table 1 sensors-24-01802-t001:** Study variables.

Baseline Variables	Primary Variables
Date of birth Gender Marital Status Level of Education Economic Level Affected Side Dominant Side Type of Injury Time Since Injury Functionally of upper limbs Cognitive impairment	Degree of disability and dependence Cognitive and perceptual impairment Mental evocation capacity Perception of quality of life Surface electromyography

## Data Availability

The raw data supporting the conclusions of this article can be made available by the authors upon valid request to the corresponding author.
